## Abstract

**Background:**

The development and implementation of a Cardiogenic Shock initiative focused on increased disease awareness, early multidisciplinary team activation, rapid initiation of mechanical circulatory support, and hemodynamic-guided management and improvement of outcomes in cardiogenic shock.

**Objective:**

The objectives of this study are (1) to collect retrospective clinical outcomes for acute decompensated heart failure cardiogenic shock and acute myocardial infarction cardiogenic shock, and compare current versus historical survival rates and clinical outcomes; (2) to evaluate Inova Heart and Vascular Institute site specific outcomes before and after initiation of the Cardiogenic Shock team on January 1, 2017; (3) to compare outcomes related to early implementation of mechanical circulatory support and hemodynamic-guided management versus historical controls; (4) to assess survival to discharge rate in patients receiving intervention from the designated shock team and (5) create a clinical archive of Cardiogenic Shock patient characteristics for future analysis and the support of translational research studies.

**Methods:**

This is an observational, retrospective, single center study. Retrospective and prospective data will be collected in patients treated at the Inova Heart and Vascular Institute with documented cardiogenic shock as a result of acute decompensated heart failure or acute myocardial infarction. This registry will include data from patients prior to and after the initiation of the multidisciplinary Cardiogenic Shock team on January 1, 2017. Clinical outcomes associated with early multidisciplinary team intervention will be analyzed. In the study group, all patients evaluated for documented cardiogenic shock (acute decompensated heart failure cardiogenic shock, acute myocardial infarction cardiogenic shock) treated at the Inova Heart and Vascular Institute by the Cardiogenic Shock team will be included. An additional historical Inova Heart and Vascular Institute control group will be analyzed as a comparator. Means with standard deviations will be reported for outcomes. For categorical variables, frequencies and percentages will be presented. For continuous variables, the number of subjects, mean, standard deviation, minimum, 25th percentile, median, 75th percentile and maximum will be reported. Reported differences will include standard errors and 95% CI.

**Results:**

Preliminary data analysis for the year 2017 has been completed. Compared to a baseline 2016 survival rate of 47.0%, from 2017 to 2018, CS survival rates were increased to 57.9% (58/110) and 81.3% (81/140), respectively (*P*=.01 for both). Study data will continue to be collected until December 31, 2018.

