#### Number of Subjects

Our goal is to include approximately 200 patients before and 200 patients after initiation of Shock team. The study group will consist of a retrospective review of all patients receiving Shock Team intervention after diagnosis with acute decompensated heart failure cardiogenic shock, or acute myocardial infarction cardiogenic shock, from January 1, 2017 until Institutional Review Board (IRB) filing of protocol. A second group will consist of current patients receiving shock team intervention.

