## Results

Preliminary data analysis for the year 2017 has been completed. Compared to a baseline 2016 survival rate of 47.0%, from 2017 to 2018, CS survival rates were increased to 57.9% (81/140) and 81.3% (26/32), respectively (*P*=.01 for both). Survival in acute MI with CS increased from 52.6% (30/57) to 75.0% (12/16) and in acute decompensated HF from 61.4% (51/83) to 87.5% (14/16). For 2017, CS threshold markers at 12 hours (lactate<3.0 mg/dL, CPO>.6 W, PAPi>1.0) overall survival was 80% (72/90), 93.6% (73/78) and 74% (71/96), respectively. For 2018, CS threshold markers at 12 hours (lactate<3.0 mg/dL, CPO>.6 W, PAPi>1.0), overall survival was 92.3% (24/36), 92% (23/25) and 85.2% (23/27), respectively. Use of RHC was associated with 14% greater survival. Decreases of 5 and 10 hours in the time to implement MCS were associated with increased survival 53.6% and 135.8%, respectively. Age was associated with survival; patient’s ≥75 years old had higher risk of death (odds ratio 3.43, 95% CI 1.20-9.78).

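### The headline preliminary survival result is misprinted in the abstract, and a P value of .01 against 2016 cannot be right for both 2017 and 2018

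*Protocol article*

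**What the plan says.** The headline result appears twice in the protocol article.

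- Abstract, Results: "from 2017 to 2018, CS survival rates were increased to 57.9% (58/110) and 81.3% (81/140), respectively".
- Main Results section: "CS survival rates were increased to 57.9% (81/140) and 81.3% (26/32), respectively".

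Both places set the two years against the same reference ("Compared to a baseline 2016 survival rate of 47.0" per cent), give no numerator or denominator for it, and attach one P value to both comparisons: "respectively (*P*=.01 for both". Neither names the test or its sides.

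The Results section then splits survival by etiology: "Survival in acute MI with CS increased from 52.6% (30/57) to 75.0% (12/16) and in acute decompensated HF from 61.4% (51/83) to 87.5% (14/16". For the 2018 12-hour markers (lactate, CPO, PAPi) it states: "overall survival was 92.3% (24/36), 92% (23/25) and 85.2% (23/27), respectively".

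On the comparator, the abstract's Methods describe a historical control group from the same institute. Number of Subjects says: "Our goal is to include approximately 200 patients before and 200 patients after initiation of Shock team". Method of Data Analysis promises a standard error and a 95% CI for any reported difference.

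**The concern.** The percentages are the same in both places but the fractions are not, so at least one version is wrong. A reader of the abstract alone would take the 2018 rate to rest on 140 patients.

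The P value raises a second question. The two years differ greatly in effect (about 11 and 34 points above 47.0%) and in size (140 and 32), so an identical P against one reference would be a coincidence. The reference is itself a sample of patients. If it was treated as known without error, the evidence for 2017 is overstated. The article's Conclusions speak of superior outcomes, and this sentence is the main numerical support for that.

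**Working it through.** **1. Fractions**

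| Place | Printed | Division |
|---|---|---|
| Abstract, 2017 | 57.9% (58/110) | 52.7% |
| Abstract, 2018 | 81.3% (81/140) | 57.9% |
| Results, 2017 | 57.9% (81/140) | 57.9% |
| Results, 2018 | 81.3% (26/32) | 81.25% |
| Results, 2018 lactate marker | 92.3% (24/36) | 66.7% |

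No whole number out of 110 gives 57.9% (63/110 = 57.3%, 64/110 = 58.2%).

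The etiology counts show which version is right:
- 2017: 30/57 + 51/83 = 81/140.
- 2018: 12/16 + 14/16 = 26/32.

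The fractions in the Results section are therefore the consistent set. The exact 95% CI for 26/32 is 64% to 93%. The lactate denominator of 36 cannot be a subset of 32 patients; 24/26 would give 92.3%, but only the source data can settle that.

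**2. Reproducing the printed P: one-sample test against a fixed 0.47**

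z = (p − 0.47) / √(0.47 × 0.53 / n), two-sided.

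- 2017, 81/140: (0.5786 − 0.47) / 0.0422 = 2.57, P=.010 (exact .011). This matches the printed value.
- 2018, 26/32: (0.8125 − 0.47) / 0.0882 = 3.88, P=.0001. This does not.
- The abstract's 58/110: (0.5273 − 0.47) / 0.0476 = 1.20, P=.23.

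**3. Two-sample test against 47% of m controls**

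z = (p − 0.47) / √[p̄(1 − p̄)(1/n + 1/m)], where p̄ is the pooled proportion. The 2016 count is not in the document, so m is an assumption. About 200 is planned for the whole pre-team group, which makes 200 an upper guide for one year.

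Example, 2017 with m = 100: p̄ = (81 + 47)/240 = 0.533, SE = 0.0653, z = 0.1086/0.0653 = 1.66, P=.096.

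| Assumed m | 2017: P | 2017: difference (95% CI, unpooled SE) | 2018: P |
|---|---|---|---|
| 50 | .185 | 10.9 points (−5.2 to 26.9) | .002 |
| 100 | .096 | 10.9 points (−1.9 to 23.6) | .0007 |
| 150 | .064 | 10.9 points (−0.6 to 22.3) | .0004 |
| 200 | .049 (Fisher .061) | 10.9 points (0.1 to 21.6) | .0003 |

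**4. What control size would give .01?**

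- 2017: P falls below .015, and so rounds to .01, at about 1,200 controls two-sided (1,194 by the pooled formula) or about 350 one-sided (349).
- 2018: P lies between .005 and .015 only for m of about 16 to 29. At those sizes the 2017 P is about .41 to .28.

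The ranges do not overlap, so no one control size gives .01 for both years.

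**5. Whole team period**

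(81 + 26)/(140 + 32) = 107/172 = 62.2%. Against 47% the two-sample P is .015, .006 and .003 for m = 100, 150 and 200, and it is below .05 from m of about 53.

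**The case against.** The strongest reply is that the abstract contains a transcription slip. The percentages are right in both places, the correct counts stand in the main text, and the results are labelled preliminary. That is fair as to cause, but an abstract is often read alone, and the slip hides that the 81.3% rests on 32 patients. It also does not explain the P value, which is the same in both places.

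Three stronger readings are tempting, and the document supports none of them.

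- A reader might infer that the 2017 value can only have come from treating 47.0% as a constant. The match is close, but neither the test nor the 2016 count is stated, and a very large control group, or a one-sided test with about 350 controls, would also round to .01. The one-sample reading is the best match, not a proven one. Likewise, 2018 against 2017 gives P=.014, but taking that as the origin of the second .01 would be a guess.
- A reader might infer that the claim of superior outcomes collapses. It is drawn from the preliminary results as a whole, not from 2017 alone. The pooled contrast and the 2018 contrast remain nominally significant for plausible control sizes. Confounding in a before/after comparison is a separate matter, which Study Type partly acknowledges.
- A reader might infer that the final analysis is planned as a test against 47.0%. No section says so: the article describes a control group, about 200 patients on each side, and differences with CIs.

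**Conclusion.** The point holds for the printed figures. Both abstract fractions are wrong for their percentages, and 24/36 is wrong for 92.3%; these findings need no assumption. That P=.01 cannot be right for both years against 2016 holds for a test against a fixed 47.0% and for the pooled two-sample test at any single control size.

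The direction of the error differs by year. For 2017 the printed P overstates the evidence: with 50 to 200 controls the two-sample P runs from .185 to .049, so the gain of 10.9 points is borderline or non-significant. For 2018 it understates the evidence (P about .002 to .0003), though on only 32 patients. These ranges rest on an assumed 2016 count, on 47.0% as printed, and on two-sided tests. The overall before/after difference (62.2% against 47%) stays nominally significant from about 53 controls.

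**What to change.** - Correct the abstract to 81/140 for 2017 and 26/32 for 2018.
- Check 24/36 against the source data and correct the count or the percentage.
- Give survivors and total for 2016.
- Name the test and its sides. Replace the shared P value with a two-sample difference, 95% CI and separate P for each year against control, in line with what Method of Data Analysis already promises for reported differences.
- Describe the 2017 gain on its own according to that result.

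This needs only data in hand and changes no design element or planned analysis. The cost is that the stated significance for 2017 becomes weaker.

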**Conclusions:**

The preliminary results of this study demonstrate that the INOVA SHOCK team approach to the treatment of Cardiogenic Shock with early team activation, rapid initiation of mechanical circulatory support, hemodynamic-guided management, and strict protocol adherence is associated with superior clinical outcomes: survival to discharge and overall survival when compared to 2015 and 2016 outcomes prior to Shock team initiation. What may limit the generalization of these results of this study to other populations are site specific; expertise of the team, strict algorithm adherence based on the INOVA SHOCK protocol, and staff commitment to timely team activation. Retrospective clinical outcomes (acute decompensated heart failure cardiogenic shock, acute myocardial infarction cardiogenic shock) demonstrated an increase in current survival rates when compared to pre-Cardiogenic Shock team initiation, rapid team activation and diagnosis and timely utilization of mechanical circulatory support.

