The implementation and utilization of a designated CS at the IHVI is an effective strategy to mitigate the consequences of cardiogenic shock. The IHVI CS team, founded in 2017, is mobilized for and directed to five goals: (1) the rapid identification of shock through early activation of the CS team and rapid collaborative decision making, (2) early right heart catheterization to facilitate invasive hemodynamic therapy tailored to the patients’ unique presentation, (3) the accelerated initiation of mechanical circulatory support, (4) minimization of vasopressor and inotropic support, and (5) meaningful recovery and survival of the patient [13]. Bi-weekly action and outcomes review are employed to track efficient methodology with the intention of eradicating significant preventable morbidity and death from CS [13]. Utilizing the best and most recent evidence and best practices, a comprehensive care pathway was developed. A six-month training process was focused on individual and team management of the aforementioned five goals, training and rehearsals were implemented to ensure the seamless execution of the adopted algorithms [13]. Prior to implementation of the Cardiogenic Shock team at the IHVI, 30-day survival was approximately 47%, assuming an alpha level of 0.5, two sided. We expect the implementation of an IHVI Shock algorithm to increase 30-day survival by 15%. Thus, 200 subjects in each group provide at least 80% power to detect a statistically significant increase in 30-day survival from 47%.

We propose to study the outcomes associated with CS patients who have been managed by the CS team at the IHVI in order to ascertain the effects on outcome and survival rate. Positive effects in outcomes and survival will indicate a positive correlation between meaningful survival and management by a multidisciplinary shock team. The database compiled from these outcomes will also serve as a clinical archive of distinctive patient characteristics and outcomes to support future evaluation and translational research. The benefit of CS management to patients is a decrease in disability and mortality post CS episode.

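### Superiority is concluded from significance tests on an incomplete cohort while collection continues, and any final comparison would reuse the same patients

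*Protocol article*

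**What the plan says.** The Hypothesis section predicts better survival, both to discharge and overall, than in 2015 and 2016. Background and Significance sets this up as a powered comparison: "200 subjects in each group provide at least 80% power to detect a statistically significant increase in 30-day survival from 47" per cent. Number of Subjects gives the target: "Our goal is to include approximately 200 patients before and 200 patients after initiation of Shock team".

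The main Results section states that "Preliminary data analysis for the year 2017 has been completed". Against a 2016 baseline of 47.0% it reports 57.9% (81/140) for 2017 and 81.3% (26/32) for 2018, with P=.01 for both. The abstract prints the same percentages and P value with other counts, 58/110 and 81/140.

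The abstract's Conclusions say that the preliminary results demonstrate that the team approach "is associated with superior clinical outcomes: survival to discharge and overall survival when compared to 2015 and 2016 outcomes prior to Shock team initiation". The abstract's Results also say: "Study data will continue to be collected until December 31, 2018".

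Method of Data Analysis lists summary statistics and differences with standard errors and 95% confidence intervals. Study Type names a raised type I error risk as a limitation of comparing with historical controls.

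**The concern.** The conclusion in the abstract is the study hypothesis in almost the same terms, and it is drawn before the cohort is complete. A later comparison on the full cohort would include every patient already tested. A positive final result would then be largely the same evidence reported twice. A null final result would follow a published claim of superiority.

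If superiority can be claimed at an early test or at a final one, the chance of a false claim exceeds the level of each single test. Testing 2017 and 2018 separately against the same baseline adds a second route to a false claim, whether or not collection continues. The investigators also know survival by era while records are still being abstracted, so it matters that eligibility and exclusions do not depend on what has been seen.

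**Working it through.** **1. The plan's own figure.** Inputs from Background and Significance: 47% survival before the team, an increase of 15%, 200 per group. I read the increase as absolute (62%) and alpha as two-sided 0.05. The document prints "assuming an alpha level of 0.5, two sided", which looks like a misprint, but 0.05 as a significance level appears nowhere in it.

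Power = Φ{[Δ√n − 1.96√(2p̄q̄)] / √(p₁q₁ + p₂q₂)}, with Δ = 0.15, n = 200, p̄ = 0.545:

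- √(2 × 0.545 × 0.455) = 0.704
- √(0.47 × 0.53 + 0.62 × 0.38) = 0.696
- (2.121 − 1.380)/0.696 = 1.064, so power is 85.6%.

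The claim of at least 80% holds on this reading, so 0.05 is a reasonable working assumption for the rest.

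**2. How much of the cohort was tested.** Main Results: 140 + 32 = 172 team patients, and 172/200 = 86% of the target. Abstract: 110 + 140 = 250, which is above the target. The abstract's counts do not match its percentages: 58/110 = 52.7%, not 57.9%, and 81/140 = 57.9%, not 81.3%. The main Results counts do match (81/140 = 57.9%, 26/32 = 81.3%), so I use those.

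**3. One early look plus a final pooled test.** With n_c shared controls and n team patients, information is I = 1/(1/n_c + 1/n). The early and final Z statistics have correlation ρ = √(I_early/I_final). The chance of at least one false positive is P(|Z₁| > 1.96 or |Z₂| > 1.96) under a bivariate normal with correlation ρ.

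Example with 200 controls, a look at 140 and a final 200: I = 82.4 and 100.0, fraction 0.824, ρ = 0.907, result 7.0%.

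The article gives neither the control size nor the final team size, so I varied both (controls 100, 200, 400; final team group 200 or 280):

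| Early look | Range over these assumptions |
|---|---|
| 2017 only (140), then final | 6.7-7.9% |
| Pooled 172, then final | 6.1-7.4% |

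**4. The two yearly tests, counted separately.** They share only the controls, so ρ = (1/n_c)/√[(1/n_c + 1/140)(1/n_c + 1/32)]. This is 0.376, 0.238 and 0.139 for 100, 200 and 400 controls.

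- The two reported tests alone: 9.4%, 9.6% and 9.7%.
- Both yearly tests plus a final pooled test (trivariate normal, simulated): 10.4-12.0%.

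Binomial simulation at 47% survival in every group agrees to within about 0.1 percentage point. A single final test stays at 5.0-5.3%.

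**5. Would the reported P value survive adjustment?** At information fraction 0.82, a constant two-look boundary is about |Z| > 2.10 (nominal P about .036). Bonferroni over three tests is .0167. A P of .01 passes both. However, for 81/140 that value is reproduced only if 47% is treated as a known constant: z = (0.5786 − 0.47)/√(0.47 × 0.53/140) = 2.57, P = .010. Against a sampled control group the unadjusted chi-square P is .049 with 200 controls and .096 with 100, and both exceed .036. For 26/32 the corresponding values are about .0003 to .0007, from 32 patients.

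**The case against.** A reader might infer that the study's overall false-positive rate is 7-12% instead of 5%. The documents do not support that as a fact about this plan. The article states no threshold for the preliminary tests, no control size at the look and no number of later tests, and it does not say that a final hypothesis test will follow. The figures are conditional, and some schedules give little more than 6%. The upper end comes mainly from testing two calendar years separately, not from continued accrual.

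Other points also stand. The results are labelled preliminary, and the conclusion speaks of association. This is an observational chart review in which nothing ties accrual or treatment to the early result, so a group-sequential boundary is an option and not a requirement. The type I error remark in Study Type concerns historical controls and cannot be read as an admission about repeated looks. The printed P of .01 would pass common adjusted boundaries, so repeated testing alone does not overturn the finding. Whether .01 is itself right is a separate question.

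It can also be said that interim looks and multiplicity belong in a full protocol or analysis plan that is not shown. That answers a complaint about missing detail. It does not answer this point, which concerns what the article states: P values and a conclusion that the hypothesis is demonstrated, from data still being collected. The sample-size statement and the primary outcome of current versus historical survival also show that a test is intended, although the analysis section is descriptive.

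**Conclusion.** The point holds in a conditional form. The article presents its superiority hypothesis as demonstrated on an incomplete cohort, 172 of about 200 planned team patients by the main Results counts, and any final comparison would reuse those patients.

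If each test is made at two-sided 0.05, the chance of at least one false-positive claim is roughly 6-8% for one early look plus a final pooled test. It is about 9-12% when the two yearly tests are counted, and the lower end of that range needs no further test at all. These ranges assume 100-400 controls and 200-280 final team patients. They take the main Results counts as correct and describe sampling error only. They say nothing about the selection bias that the article concedes. The excess is modest, but the correction is cheap.

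**What to change.** - **Abstract (Results) and main Results:** reconcile the two sets of counts. Present the yearly figures as descriptive estimates with confidence intervals, and remove the P values.
- **Abstract (Conclusions):** replace the superiority conclusion with a statement that survival to date was higher.
- **Method of Data Analysis:** state that the hypothesis is tested once, on the complete cohort after December 31, 2018. State the significance level, correcting the printed 0.5 if it is a misprint. State that eligibility and exclusions are fixed in writing regardless of the preliminary result.
- **If the preliminary P values are kept as evidence:** specify the number and type of tests and how the error is shared among them.

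This needs changes of wording only and no new data. The downside is that the preliminary report can no longer claim superiority.

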**Conclusions:**

The preliminary results of this study demonstrate that the INOVA SHOCK team approach to the treatment of Cardiogenic Shock with early team activation, rapid initiation of mechanical circulatory support, hemodynamic-guided management, and strict protocol adherence is associated with superior clinical outcomes: survival to discharge and overall survival when compared to 2015 and 2016 outcomes prior to Shock team initiation. What may limit the generalization of these results of this study to other populations are site specific; expertise of the team, strict algorithm adherence based on the INOVA SHOCK protocol, and staff commitment to timely team activation. Retrospective clinical outcomes (acute decompensated heart failure cardiogenic shock, acute myocardial infarction cardiogenic shock) demonstrated an increase in current survival rates when compared to pre-Cardiogenic Shock team initiation, rapid team activation and diagnosis and timely utilization of mechanical circulatory support.

